#### Inclusion and exclusion criteria

Inclusion criteria are as follows: (1) adults aged 17 years or above; (2) DSM-5 [50] diagnosis of AN or ARFID; (3) BMI of equal to or less than 16.0 kg/m^2^; (4) in need of intensive treatment because of either rapid weight loss, and/or evidence of system/organ failure/medical instability and/or unsuccessful outpatient treatment, as defined by NHS England [51]; and (5) have mental capacity to give informed consent to participate in the study. Exclusion criteria are as follows: (1) individuals with insufficient knowledge of English to complete study assessments or understand treatment; (2) individuals with severe learning disabilities; (3) individuals with a severe medical or psychiatric (co)morbidity (e.g. psychosis, substance dependence) requiring treatment in its own right; and (4) those living too far away from day patient treatment (and where no alternative arrangements for regular attendance at day patient treatment can be made).

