#### Sample size

The sample size calculation is based on a one-sided non-inferiority test at 97.5% confidence. Previous studies suggested a standard deviation for within-group BMI at 12 months of 2.3 kg/m^2^ [19, 38]. Based on Herpertz-Dahlmann et al. [19], we defined our non-inferiority threshold as a 0.75 kg/m^2^ decrease in BMI for stepped care relative to IP-TAU. If there is truly no difference between stepped care and IP-TAU, then 198 participants per trial arm are needed to be 90% sure that the lower limit of a one-sided 97.5% confidence interval (or equivalent a 95% two-sided confidence interval) for the difference will be above the non-inferiority limit of −0.75. To account for the precision gain due to including baseline BMI in the modelling, we applied a deflation factor (0.78, based on a pre-post correlation of 0.47, [38]) to the estimated sample size [52]. We also inflated the requirement to account for 20% dropout at 12 months based on our previous studies [53, 54]. This gave a final sample size requirement of 193 per trial arm (*n* = 386 in total).

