### Data analysis

A detailed statistical analysis plan will be developed by the trial statisticians whilst maintaining full blind and agreed with the research team and Data Monitoring and Ethics Committee before the end of the internal pilot. Briefly, all formal comparisons of the two care pathways will follow the intention-to-treat principle. For continuous clinical outcomes variables, such as BMI, linear mixed models will be fitted to the outcome measures at 6 and 12 months to estimate the trial arm differences. The fixed part of these models will contain the explanatory variables of interest (trial arm, time and an interaction term) and also baseline values of outcome variables and randomisation stratifiers, as these variables are known to explain variability in outcome. To account for correlation between the repeated measures at 6 and 12 months, a subject-varying random intercept will be included. For non-continuous outcomes, relevant generalised linear mixed models will be fitted. Results are valid under a missing at random (MAR) missing data generating mechanism that allows earlier outcome values to predict missingness of later ones. In the presence of missing data, should we find that the assumptions underlying the mixed modelling approach are not realistic, then an alternative, more flexible approach such as multiple imputation will be used instead.

To judge non-inferiority of the stepped care approach in terms of the primary outcome (BMI at 12 months), a two-sided 95% confidence interval of the trial arm difference in this clinical measure will be generated and this interval compared with the non-inferiority threshold (0.75 kg/m^2^ decrease in BMI). The threshold defines a region for the trial arm difference in BMI in which the stepped care day patient approach would be considered non-inferior to IP-TAU. To confirm the non-inferiority hypothesis, the whole 95% confidence interval would need to lie within this region. Supplementary subgroup analyses will estimate care pathway differences in treatment-completer populations (defined using the minimal and full treatment completion criteria described previously) to investigate the impact of any treatment non-completion on the non-inferiority assessment. In this context, methods from the causal inference field, e.g. inverse probability weighting, will be used to adjust for variables driving both treatment completion and primary BMI outcome [75]. No other subgroup analyses are planned.

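### A random intercept alone makes the deciding 12-month interval depend on equal 6- and 12-month BMI variance, an assumption the protocol does not support and could drop at almost no cost

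*Protocol article*

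**What the plan says.** Under Data analysis, the protocol article says that "linear mixed models will be fitted to the outcome measures at 6 and 12 months". The fixed part contains arm, time, their interaction, the baseline value of the outcome and the randomisation stratifiers. For the dependence between the two visits it says: "To account for correlation between the repeated measures at 6 and 12 months, a subject-varying random intercept will be included". It does not say whether the residual variance is common to both visits, and it names neither an unstructured covariance nor a robust standard error. It lists no baseline-by-time term, but does not exclude one.

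The same section judges non-inferiority on the two-sided 95% interval for the 12-month arm difference, which must lie wholly on the acceptable side of the margin. Under Sample size, the margin is fixed as follows: "we defined our non-inferiority threshold as a 0.75 kg/m^2^ decrease in BMI for stepped care relative to IP-TAU". That section gives one SD, for 12 months only: "Previous studies suggested a standard deviation for within-group BMI at 12 months of 2.3" kg/m². No 6-month SD appears anywhere in the article.

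The section describes itself as brief and refers to a detailed statistical analysis plan, which is not at hand. It also offers a fallback: if data are missing and the mixed-model assumptions prove unrealistic, a more flexible method such as multiple imputation would be used.

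**The concern.** With two follow-up visits, a subject random intercept plus one residual variance is compound symmetry: one total variance shared by both visits, and one covariance. The arm-by-time interaction gives each visit its own arm difference, but the standard errors of both differences are built from the same pooled variance. If the true variances differ, the 12-month interval is mis-sized even with no missing data.

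The consequence is not symmetrical for a non-inferiority trial. If BMI spread grows from 6 to 12 months, the 12-month interval is too narrow and an inferior pathway is declared non-inferior more often than 2.5% of the time. If spread shrinks, the interval is too wide and power is lost. Because this single interval carries the primary conclusion, its error rate should not depend on an assumption that the analysis does not need.

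**Working it through.** **Inputs from the protocol article, Sample size section.** One-sided alpha 0.025; margin 0.75 kg/m²; 12-month SD 2.3 kg/m²; true difference 0; power 90%; pre-post correlation 0.47 (deflation factor 0.78); 20% dropout at 12 months; 193 per arm.

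**Inputs the article does not give.** The ratio r = SD at 6 months / SD at 12 months, both after baseline adjustment, is varied from 0.7 to 1.2. A within-person correlation of 0.7 is assumed for the simulation only.

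**Step 1: the plan's own figure.** n per arm = 2 × (1.960 + 1.2816)² × 2.3² / 0.75² = 197.6, so 198. The deflation is 1 - 0.47² = 0.779, stated as 0.78. Then 198 × 0.78 / 0.80 = 193.05, so 193 per arm. The stated sample size reproduces.

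**Step 2: the 12-month interval if the 12-month variance is estimated on its own.**
- Adjusted SD = 2.3 × √(1 - 0.47²) = 2.03.
- Analysed per arm = 193 × 0.80 = 154.4.
- SE = 2.03 × √(2/154.4) = 0.231.
- 95% CI width = 2 × 1.96 × 0.231 = 0.906.
- Power = Φ(0.75/0.231 - 1.96) = 90.1%.

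**Step 3: the same interval under a random intercept with one residual variance.** With complete data, the pooled variance is the average of the two visit variances, so

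model SE / correct SE = √((r² + 1)/2).

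At a true difference of -0.75, the one-sided error is 1 - Φ(1.96 × ratio). For r = 0.7 the ratio is √(1.49/2) = 0.863 and the error is 1 - Φ(1.692) = 4.5%. Applying the ratio to the SE from Step 2 gives:

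| r | SE ratio | CI width | One-sided error | Two-sided coverage | Power at true difference 0 |
|---|---|---|---|---|---|
| 0.7 | 0.863 | 0.782 | 4.5% | 90.9% | 94.0% |
| 0.8 | 0.906 | 0.820 | 3.8% | 92.4% | 92.9% |
| 0.9 | 0.951 | 0.862 | 3.1% | 93.8% | 91.6% |
| 1.0 | 1.000 | 0.906 | 2.5% | 95.0% | 90.1% |
| 1.1 | 1.051 | 0.952 | 2.0% | 96.1% | 88.2% |
| 1.2 | 1.105 | 1.000 | 1.5% | 97.0% | 86.0% |

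**Step 4: check by simulation.** REML fits, 193 per arm, true 12-month difference -0.75, 20% of 12-month values missing completely at random, 700 runs per setting. Outcomes were generated after baseline adjustment, so the two fits differ only in covariance structure.

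| r | False non-inferiority, compound symmetry | False non-inferiority, unstructured |
|---|---|---|
| 0.7 | 5.1% | 1.7% |
| 0.8 | 3.9% | 2.3% |
| 1.0 | 2.3% | 2.1% |
| 1.2 | 0.9% | 2.1% |

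Monte Carlo error is about 0.6 percentage points at a rate of 2.5%. At r = 0.7 the compound-symmetry model reported an SE of 0.185 against an empirical 0.219; the unstructured model reported 0.219 against 0.217. The simulation agrees with the formula in direction and approximate size. The point estimate was not biased in these runs. They do not cover dropout that depends on 6-month BMI.

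**The case against.** The strongest reply is that nothing here shows the interval to be wrong. That stands. A reader might infer that the interval will be too narrow and non-inferiority declared too easily, but the article does not support this. It gives no 6-month SD; at r = 1 the width is exactly right, and above 1 the error is conservative. Within 10% either side of equality the width changes by only about 5%.

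One might argue for widening from the entry criterion, "BMI of equal to or less than 16.0" kg/m². A cap at entry explains why spread grows from baseline to follow-up. It says nothing about growth from 6 to 12 months. The Background section quotes mean stays of 86.3 days for day treatment, and of 105.6 days (Europe) and 116 days (UK audit) for inpatient treatment. Many patients may therefore finish intensive treatment before 6 months, with much of the spread already present. Later relapse and recovery could widen it further, but that is conjecture.

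It is also fair to say that a common residual variance is inferred. A random intercept can be combined with visit-specific residual variances, and the analysis plan may specify them. Silence on a baseline-by-time term does not exclude one either. This makes the point conditional but does not remove it: the article names a specific structure, and its usual fit has one residual variance.

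The multiple-imputation fallback does not answer the point. It is tied to missing data, whereas unequal variances mis-size the interval with complete data too.

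**Conclusion.** The point holds in conditional form. If the random intercept is fitted with one residual variance, the interval that decides non-inferiority rests on equal baseline-adjusted BMI variance at 6 and 12 months, and the article offers no justification for that. The one-sided error would be about 3% to 5% for SD ratios of 0.9 down to 0.7, 2.5% at equality, and 2.0% to 1.5% for ratios of 1.1 to 1.2. Which of these applies cannot be known from the article.

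The figures assume the protocol's own SD, correlation, dropout and sample size. The formula is for complete data; the simulation adds a within-person correlation of 0.7 and values missing completely at random. The reading that the interval already has the wrong width, or favours stepped care, goes beyond the document. The sample size calculation is unaffected. This is a change that should be made because it is nearly free, not a demonstrated error that must be corrected.

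**What to change.** In the analysis section, and in the statistical analysis plan if it does not already say so:

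- Replace the subject random intercept with an unstructured 2x2 covariance for the 6- and 12-month outcomes. Alternatively, keep the random intercept and allow a separate residual variance at each visit. One or the other is enough; with two visits, a random intercept on top of a full unstructured matrix is over-parameterised.
- Add a baseline BMI-by-time term, so that the baseline slope may differ between visits.
- State that the non-inferiority decision uses the 12-month arm contrast and its 95% interval from this model.

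The cost is one extra variance parameter (three instead of two) and one extra slope. No further patients or data are needed. On the protocol's inputs the sample size stays at 193 per arm and planned power at about 90%. The change should be made before unblinded outcome data are seen.

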#### Economic evaluation

The economic evaluation will take the NHS/personal social services perspective preferred by the National Institute for Health and Care Excellence (NICE) and shown in previous AN studies to constitute over 90% of total societal costs. Service use data will be collected using the Adult Service Use Schedule (AD-SUS), designed for use in adult populations with mental health conditions [71, 72] and modified for AN on the basis of relevant literature and clinical expertise. The AD-SUS is used to assess the number and length of contacts with various health and social care services and professionals, plus prescribed medications, over a period of time appropriate for each individual study. The DAISIES AD-SUS will be used at baseline to collect use of services in the previous 6 months and at the 6- and 12-month follow-ups to collect use of services since the previous interview. In this way, the full period from baseline to the 12-month follow-up will be covered. The AD-SUS is commonly administered in interview format. However, to avoid unblinding the research assessors, use of hospital services (inpatient, day patient, outpatient and Accident & Emergency) will be reported by participants using a self-report version of the AD-SUS. All remaining service use (i.e. community services and prescribed medications) will be collected in interview. This is to improve recall accuracy, whilst ensuring that the researchers remain blinded. In addition, the collection of data on use of hospital services from clinical records at each site will be piloted at baseline and, if successful, implemented at each follow-up. The self-report data will be secondary to the clinical records data and will be used where clinical data cannot be provided. Nationally applicable unit costs will be applied to all services, including the inpatient and day patient-based interventions [76, 77]. To supplement these data, Hospital Episode Statistics (HES) from NHS Digital (for participants from England) and Information Services Division (ISD; for participants from Scotland) will also be requested and incorporated if data is received in a timely fashion.

Cost-effectiveness will be explored at the 12-month follow-up in terms of QALYs measured using the EQ-5D-5L [70], with a sensitivity analysis using the primary clinical measure of outcome (BMI), given the limited evidence available for the validity of the EQ-5D-5L in ED populations. QALYs will be calculated by applying appropriate utility weights to health states [78] and using the total area under the curve approach with linear interpolation between assessment points [79].

Mean differences in costs and 95% confidence intervals will be obtained by nonparametric bootstrap regressions to account for the non-normal distribution often found in economic data. Cost-effectiveness analyses will be undertaken irrespective of whether non-inferiority is demonstrated, since exploration of the joint distribution of costs and effects is recommended to represent uncertainty [80] and to help interpret the economic results [81]. Incremental cost-effectiveness ratios (ICERs) will be calculated if higher costs and better outcomes are found in either the stepped care day patient approach or IP-TAU group. Uncertainty around cost-effectiveness estimates will be explored using cost-effectiveness planes and cost-effectiveness acceptability curves (CEACs) based on the net-benefit approach [82]. All economic analyses will be adjusted in line with the clinical approach (baseline values of the variables of interest and randomisation stratifiers). Missing economic cost and outcome data will be imputed using multiple imputation methods by using chained equations, under the assumption that these data were missing at random [83].

#### Qualitative analysis

Qualitative data will be analysed using the Framework Approach [84] to facilitate analysis within and between individual cases and groups of participants. The thematic framework will draw on a priori issues around perceived mechanisms of impact, implementation and context, but be responsive to emergent and analytical themes. Once applied to individual transcripts, data will be charted to map and interpret the data set as a whole. Qualitative process data will be analysed prior to the outcome data, but any insights will not be communicated to the wider team until the RCT outcomes are known.

### Patient and public involvement

The initial study proposal was discussed with 12 patients with severe AN who had experience of day treatment, inpatient treatment or both. Patients strongly endorsed the design of the present study, in particular the stepped care aspect, as this was felt to offer individually tailored care. Measures of treatment motivation, perceived coercion, social support and loneliness were added to the study, based on patient feedback. Two patients and a carer reviewed and commented on the final proposal. Three people (two patients, one carer) will become patient and public involvement (PPI) representatives. Additionally, qualitative semi-structured interviews with PPI representatives (who have received intensive treatments for severe anorexia nervosa or a related disorder and carers of such patients) will be conducted to inform recruitment strategies and study implementation.

## Ethics and dissemination

### Ethics and safety aspects

Ethical approval was received from Wales Research Ethics Committee 5 (Reference: 20/WA/0072), and all recruiting sites will obtain individual approvals through their local Research and Development departments. Written informed consent to participate in the study will be obtained from all participants by the research team. It will be made clear to participants that they can withdraw from the study at any time without justification. In addition, participants will be informed that if they withdraw from the study intervention only, the research team will continue to make efforts to obtain follow-up data, unless requested otherwise.

The Trial Management Group will be responsible for the day-to-day management of the trial. The trial will also be overseen by two independent committees, the Data Monitoring and Ethics Committee and the Trial Steering Committee (as described above). All committees will be responsible for ensuring the trial is run in compliance with the trial protocol, the Declaration of Helsinki, the Principles of Good Clinical Practice (ICH-E6 guideline) and in accordance with all applicable regulatory requirements. Any substantial protocol amendments will be first discussed with the Sponsor and the National Institute for Health and Care Research (NIHR), before submitting an amendment to the Research Ethics Committee. Standard King’s College London insurance and NHS indemnity arrangements apply to this study.

To ensure patient safety and inform treatment step-up/step-down, whilst in treatment, weekly decision tools will be conducted by the clinical team, as described above. The decision tool will comprehensively assess medical risk, using objective indicators of nutritional status, cardiovascular function, laboratory parameters, other physical risk indications and psychosocial risk. A risk reference committee will also be established for discussion or advice on any risk concerns.

Patients enrolled into the study are covered by indemnity for harm arising from the conduct of the study through the standard NHS indemnity arrangements. King’s College London has insurance to cover for harm arising from the management and design of the protocol.

### Dissemination policy

The results of this study will be reported and disseminated at national and international conferences and in peer-reviewed open-access scientific journals. We will also disseminate findings through relevant websites and social media. Finally, we will work closely with NHS England to implement findings.

An Authorship Policy will be developed by the Trial Management Group to determine the criteria that are required to be met for authorship. For each publication, authorship will be decided by all of the people involved in conducting the study with reference to the Authorship Policy. No professional writers will be used.

## Discussion

Inpatient and/or day patient treatment are recommended for severe AN by international guidelines [10, 85]. However, there is limited previous research regarding clinical outcomes and the cost-effectiveness of intensive treatment approaches for severe AN [19, 21, 26]. The DAISIES trial is the first RCT to compare inpatient care to a stepped care day patient approach for adults with severe AN. This is a complex trial which will take participating services out of their ‘comfort zone’ and require them to substantially change their clinical practice and service protocols (e.g. by stepping patients down from inpatient to day patient treatment early and accepting more unwell patients into day treatment). It is for these reasons that the internal pilot and qualitative aspects of the trial will be of great importance to the ongoing day-to-day implementation of trial procedures, e.g. developing effective recruitment strategies. In addition, we intend to start the trial during the Covid-19 pandemic, with services running at a reduced capacity, which poses additional challenges. Despite these challenges, it is hoped that the results of this study will provide a rigorous evaluation of two intensive treatment approaches which will inform future NICE and international treatment guidelines and service provision.

## Trial status

Protocol version 6, 15 June 2021.

Participant recruitment and data collection for this trial commenced in November 2020 and is expected to run until April 2022.

Sponsor: King’s College London (KCL) is the lead sponsor and South London and Maudsley NHS Foundation Trust is the co-sponsor for this study. Sponsor contact details are as follows: [name], [name]. The sponsors will act as the data controllers for this study.

## Data Availability

The trial protocol will be available upon request from the Principal Investigator and the full study report, anonymised data set and statistical code will be made available 24 months after the final data set has been obtained.

## Abbreviations

AD-SUS: Adult Service Use Schedule
AN: Anorexia nervosa
AQ-10: Autism Spectrum Quotient
ARFID: Avoidant restrictive food intake disorder
BMI: Body mass index
CEAC: Cost-effectiveness acceptability curves
CIA: Clinical Impairment Assessment
DASS-21: Depression, Anxiety and Stress Scales-Version 21
DSM: Diagnostic and Statistical Manual of Mental Disorders
ED: Eating disorder
EDE: Eating Disorder Examination
EDE-Q: Eating Disorder Examination Questionnaire
EDE-QS: Eating Disorder Examination Questionnaire Short
EDSIS: Eating Disorder Symptom Impact Scale
HES: Hospital Episode Statistics
ICER: Incremental cost-effectiveness ratios
IP-TAU: Inpatient treatment as usual
ISD: Information Services Division
KCTU: King’s Clinical Trials Unit
MAR: Missing at random
MSPSS: Multidimensional Perceived Social Support Scale
NHS: National Health Service
NICE: National Institute for Health and Care Excellence
NIHR: National Institute for Health and Care Research
OCI-R: Obsessive Compulsive Inventory-Revised
PCS: Perceived Coercion Scale
PPI: Patient and public involvement
QALY: Quality-adjusted life-years
RCT: Randomised controlled trial
TESS: Therapeutic Environment Scale
VAS: Visual analogue scale
WSAS: Work and Social Adjustment Scale
